## Results

### Demographics

In total, 43 participants were recruited with a mean age of 11.82 (SD 2.81) years. Among these, 28 (65%) were male and 15 (35%) were female. Of the 43 participants, 18 (42%) were diagnosed with ADHD and 25 (58%) participants were considered controls (non-ADHD). Approximately 30 participants (70%) completed the first part of the pilot phase remotely.

### Neuropsychological Data

Neuropsychological data were obtained from 30 participants. They were evaluated using WISC-V by the psychologist of the ADHD360 team or by an approved national body within the last 2 years. Among the 30 participants, 10 (33%) were diagnosed with ADHD and 20 (67%) were considered as healthy controls (non-ADHD). There were 21 males (70%) and 9 females (30%). In the ADHD group, all participants were male, whereas in the non-ADHD group, 11 (55%) were male and 9 (45%) were female. The mean age of the screened participants was 11.40 (SD 2.85) years. In the ADHD group, the mean age of the participants was 12.90 (SD 2.64) years, whereas that of the participants in the non-ADHD group was 10.65 (SD 2.70) years.

According to the data from the first neuropsychological assessment, the mean score in the figure weights subtest in the ADHD group was 14.00 (SD 5.79), whereas the median score of this subtest in the non-ADHD group was 19 (IQR 13-24). The mean scores in the subtests block design, similarities, digit span, coding, and vocabulary are presented in Table 1.

The mean score of the participants in the inattention subscale of the ADHD Rating Scale-IV was 12.70 (SD 7.04), whereas that in the hyperactivity-impulsivity subscale was 10.97 (SD 6.65). In the full group of participants, the mean total score was 23.67 (SD 12.56). The mean scores on the ADHD Rating Scale-IV obtained by grouping the participants based on their diagnosis are presented in Table 2.

**Table 1 table1:** Mean scores of the study participants in the subtests block design, similarities, digit span, coding, and vocabulary.

WISC^a^ subtest	ADHD^b^, mean (SD)	non-ADHD, mean (SD)
Block design	19.60 (4.30)	22.85 (8.02)
Similarities	22.00 (7.45)	23.50 (9.05)
Digit Span	18.30 (4.03)	19.75 (6.26)
Coding	27.80 (9.69)	32.20 (13.46)
Vocabulary	20.20 (5.55)	23.05 (8.17)

^a^WISC: Wechsler Intelligence Scale for Children.

^b^ADHD: attention deficit hyperactivity disorder.

**Table 2 table2:** Mean scores of the participants on the ADHD Rating Scale-IV.

ADHD^a^ Rating Scale-IV	ADHD, mean (SD)	non-ADHD, mean (SD)
Inattention subscale	18.50 (5.84)	9.80 (5.74)
Hyperactivity-impulsivity subscale	15.30 (6.58)	8.80 (5.67)
Total score	33.80 (9.94)	18.60 (10.62)

^a^ADHD: attention deficit hyperactivity disorder.

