#### Remote Participation

All the procedures are identical to those followed during in-person participation, apart from the interactions with the serious game that are done remotely from their home using their personal computers.

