#### ML Methodology

State-of-the-art ML algorithms are used to analyze labeled gameplay data. Specifically, we attempt to classify game-generated data based on the user’s known label (ADHD or non-ADHD). All in-game events of a gameplay session are recorded to form a time series that one can use to reconstruct the whole gameplay session. These events correspond to player actions and environmental parameters, such as performing a jump/move, left or right moving action, obstacle collision, and coin collection. Informative feature extraction is performed by splitting players’ time series depending on the game level. Different feature extraction techniques are assumed for each level depending on its type. In the main runner game, several aggregates are calculated by capturing different events during the gameplay (ie, movement of a player or the ability to avoid obstacles). In the mini games, feature extraction is based on the characteristic game mechanics and events of the respective mini game. The final feature vector of each player is produced by concatenating the individual-level feature vectors.

A schema that includes train-test splitting with a 75:25 split ratio, *k*-fold cross-validation (CV) with k=3, an ML pipeline, and data evaluation was designed for experimental purposes. The train-test splitting is used for model specification (eg, feature selection and model tuning), model selection, and training of the final model. Modeling decisions are made on the training set. Thus, the test set is used only to evaluate and report the statistics of the algorithm’s performance. The purpose of 3-fold CV is to fine-tune the hyperparameters of the supervised learning algorithms (classifiers) that we investigate.

For each classifier, an ML pipeline was designed to include the following procedures: (1) removal of features with 0 variance, (2) univariate feature selection according to a statistical criterion (ANOVA *F* value between label and feature), (3) principal component analysis for dimensionality reduction, and (4) classifier training. Therefore, the hyperparameters of all the steps are tuned (eg, the number of components in principal component analysis) in the 3-fold CV process. The *F1* score is used as the optimization criterion in the 3-fold CV, and the best configuration of each method's pipeline is then used on the entire training set (fully trained pipeline).

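### The classifier has no age or sex control and its sample is not described by age and sex, so its accuracy cannot be separated from a demographic signal

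*Protocol article*

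**What the plan says.** **Analysis.** The ML Methodology section states: "Specifically, we attempt to classify game-generated data based on the" known label of the player. Features are aggregates of in-game events by level, joined into one vector per player. The section then sets out variance filtering, univariate selection, principal components, eight classifiers, 3-fold tuning and a 75:25 split. It mentions no age or sex term, stratified split, matching, restriction or demographic benchmark. The inclusion criteria admit ages 7 to 16 and state no matching.

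**Group composition.** The Neuropsychological Data section gives the only breakdown by diagnosis. "Among the 30 participants, 10 (33%) were diagnosed with ADHD and 20 (67%) were considered as healthy controls (non-ADHD"). On sex: "In the ADHD group, all participants were male, whereas in the non-ADHD group, 11 (55%) were male and 9 (45%) were female". On age: "In the ADHD group, the mean age of the participants was 12.90 (SD 2.64) years". Controls averaged 10.65 years (SD 2.70). For all 43 recruits, the Demographics section gives sex, age and diagnosis only as separate totals; on sex: "Among these, 28 (65%) were male and 15 (35%) were female".

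**Classifier sample.** The Gameplay Data section says that 30 of the 43 participants had usable game data. It gives no age or sex for them.

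**Claim.** The abstract's conclusions and the Discussion both credit the platform with a marked ability to tell ADHD from non-ADHD play. The Discussion's limitations do not include age or sex imbalance.

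**The concern.** Age and sex may plausibly affect how a child plays a runner game: reaction time, practice with games and motor control all bear on moves, collisions and coins. The documents give no data on this, so it is an assumption. If it holds and the diagnostic groups also differ in age or sex, a classifier fed only gameplay can earn accuracy by recovering those traits indirectly. It does not need age or sex as inputs.

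What is at stake is the reading of the headline. Accuracy is offered as evidence of an ADHD-specific pattern and of value as a screening aid. Without a demographic comparator, the same figure is compatible with an ADHD signal, an age or sex signal, or a mixture. Performance in a population balanced on age and sex could then be lower than reported.

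**Working it through.** **1. Check the published ages.** Inputs from Neuropsychological Data: ADHD n=10, mean 12.90, SD 2.64; non-ADHD n=20, mean 10.65, SD 2.70. Weighted mean: (10×12.90 + 20×10.65)/30 = 11.40. Total SD from within- plus between-group variation: 2.85. Both match the article: "The mean age of the screened participants was 11.40 (SD 2.85) years".

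**2. Imbalance in that subset.**
- Age: 12.90 − 10.65 = 2.25 years. Welch t = 2.25/√(2.64²/10 + 2.70²/20) = 2.25/1.030 = 2.18, p=0.042. The pooled 95% CI is 0.12 to 4.38.
- Sex: 10/10 versus 11/20 male, Fisher p=0.013.

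**3. Is this the classifier's sample?** No.
- In Table 3, logistic regression has zero precision and recall with accuracy 0.5714, so it called every child non-ADHD. 0.5714 = 12/21, which leaves 9 ADHD in training.
- In Table 4, naïve Bayes has recall 1.00 and precision equal to accuracy at 0.42, so it called every child ADHD. 3/7 = 0.429, which gives 3 ADHD in the test set.
- 9 + 3 = 12 ADHD at least, against 10 in the neuropsychological subset.
- The sets must overlap: only 43 − 30 = 13 children lie outside the neuropsychological subset, so at least 30 − 13 = 17 of the gameplay children lie inside it.

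(The tables fit 21 and 7 children while the text gives 22 and 8; that is a separate matter.)

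**4. What the totals imply for sex in all 43.** Subtract the subset from the cohort: males 28 − 21 = 7, females 15 − 9 = 6, ADHD 18 − 10 = 8, controls 25 − 20 = 5. Six girls cannot all be among five controls, so 1 to 6 of the 18 ADHD children are girls.

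| ADHD girls | ADHD male | Control male | Fisher p |
|---|---|---|---|
| 1 | 17/18 | 11/25 | 0.0009 |
| 6 | 12/18 | 16/25 | 1.0 |

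**5. What the totals imply for age in all 43.** Inputs: mean 11.82, SD 2.81 for the 43; mean 11.40, SD 2.85 for the 30.
- Mean of the other 13: (43×11.82 − 30×11.40)/13 = 12.79.
- Their sum of squares: 42×2.81² − 29×2.85² − 30×(11.40−11.82)² − 13×(12.79−11.82)² ≈ 78.6.
- Let D be the ADHD minus control mean difference among the 13. Then (8×5/13)×D² ≤ 78.6, so |D| ≤ 5.05 years.
- With D=0, the ADHD mean is (129 + 8×12.79)/18 = 12.85 and the control mean is (213 + 5×12.79)/25 = 11.08, a gap of 1.77.
- The gap changes by (8/18)(5/13) + (5/25)(8/13) = 0.294 per unit of D. Range: 1.77 ± 0.294×5.05 = 0.29 to 3.26 years.
- Allowing for rounding of the published figures, the minimum is still 0.25, so the sign does not change.

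**6. Accuracy to be explained.** The support vector machine's cross-validated accuracy is 0.667, against a majority rate of 0.571 (12/21). Its test accuracy of 0.85 fits 6/7, whose exact 95% interval is 0.42 to 1.00.

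**The case against.** The strongest objection is that the striking imbalance belongs to another sample. The all-male, older ADHD group is 10 of the 18 ADHD children. The gameplay set holds at least 12, and the full ADHD group certainly includes at least one girl. At one end of the possible range the sexes are balanced across the 43. This stands: strong imbalance in the classifier's sample is possible but not shown.

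Stronger readings that a reader might infer, and why the documents do not support them:

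- *The classifier merely detects older boys.* Nothing reported shows that. The model never receives age or sex, and equal accuracy from a demographic rule would not prove that the model took that route. The supportable statement is that the two explanations cannot be separated.
- *A rule based on age and sex would match the model.* In the neuropsychological subset, calling every boy ADHD scores 19/30 = 0.633, below that mix's own majority rate of 20/30 = 0.667. Adding a best-chosen age cutoff gives about 0.76, but only under assumed normal ages and with age independent of sex among controls. Neither figure estimates anything for the gameplay set. In the full 43 the boy-only rule could score from (12+9)/43 = 0.49 to (17+14)/43 = 0.72.
- *Home versus on-site play separates the groups.* The article says that remote play was done "apart from the interactions with the serious game that are done remotely from their home using their personal computers" and that about 30 children completed the first part remotely. It does not say that the rest played on site; the Discussion treats the other 13 as dropouts. Mode may not have varied at all.

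It is also fair that this is a pilot, that the analysis is called preliminary, and that more data are requested. That tempers the claim but does not name this limitation, and the conclusions are still worded as discrimination of ADHD.

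**Conclusion.** The concern holds in a limited form. The plan describes no age or sex control, and the article does not give the age and sex of the classifier's sample by class. The one subset that is described is imbalanced on both (10/10 versus 11/20 male; 2.25 years). In the recruited cohort the ADHD group is older by about 0.3 to 3.3 years, and its male share is never below that of controls, though the two may be nearly equal. These ranges assume that the neuropsychological subset is nested in the 43 and that the published means, SDs and counts are right.

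The size and even the presence of imbalance in the gameplay set are not known. It follows that the accuracies of 0.667 and 0.85 cannot be attributed specifically to ADHD. It does not follow that there is no ADHD signal, or that the model would fail elsewhere.

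**What to change.** 1. Report age and sex by class for the gameplay set, split by training and test, and play mode too if it varied.
2. Fit an age-and-sex-only model on the same folds and the same test split. Attribute discrimination to gameplay only for the gain over that benchmark, with its uncertainty.
3. Give a boys-only result, labelled descriptive.
4. State the imbalance, and the lack of control for it, as a limitation, and word the conclusion to match.
5. In further recruitment, frequency-match controls to ADHD participants on sex and age band.

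Residualising game features on sex within folds should not be required: if nearly all ADHD players are boys, it could strip out diagnostic signal as well.

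Cost: a few extra model runs and one table from data already held, and somewhat slower control recruitment if matched. With about 21 training and 7 test children the benchmark and boys-only results will be imprecise, and the headline may shrink.

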### Gameplay Data

Following the methodology described above, we present the results of a preliminary analysis of gameplay data collected during pilot trials. Gameplay data were collected from all recruited participants. However, technical difficulties (ie, unstable internet connection and game installation issues) led to insufficient or no data generation in 13 of the 43 participants (30%). Therefore, gameplay data collected from 30 (70%) participants were used in the following preliminary analysis. We comprehensively describe the CV results for a training set consisting of data collected from 22 of the 30 participants (73%) as well as the selection of the best model. Subsequently, we evaluate the predictive performance on a test set consisting of data gathered from 8 (27%) participants using point estimates and CIs.

A graphical illustration of the CV *F1* results for each learning method is shown in Figure 2. Furthermore, detailed results of the *F1* score and the other performance measures for the CV procedure are given in Table 3.

Most classifiers achieved an *F1* score above 0.5. We observed significant overfitting for RF, kNN, and NB, with a difference of 0.1 between the training and validation scores. The test performance scores are given in Table 4.

The previously mentioned models seem to be substandard solutions for this classification problem, with all of them dominated by LogReg, SGD, SVM, and PAC. The latter models feature a tradeoff between validation performance and goodness of fit. Among these methods, we selected SVM for the following reasons: (1) It achieves the highest validation *F1* score (0.66). (2) Although SGD achieves the same validation score as SVM, the latter also achieves a better fit with a difference of approximately +0.07 between training and validation, which is approximately –0.09 for the former.

Even though the results are indicative of the potential that ML has in the domain of ADHD prediction based on gameplay data, we presume that experimenting with a larger data set could give more accurate and concrete conclusions.

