**Results:**

A total of 43 participants were recruited for this study, where 18 were diagnosed with ADHD and the remaining 25 were controls. Initial neuropsychological assessment confirmed that the participants in the ADHD group showed a deviation from the participants without ADHD characteristics. A preliminary analysis of collected data consisting of 30 gameplay sessions showed that the trained ML models achieve high performance (ie, accuracy up to 0.85) in correctly predicting the users’ labels (ADHD or non-ADHD) from their gameplay session on the ADHD360 platform.

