**Conclusions:**

ADHD360 is characterized by its notable capacity to discriminate player gameplay behavior as either ADHD or non-ADHD. Therefore, the ADHD360 platform could be a valuable complementary tool for early ADHD detection.

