### Analysis

#### Statistical Analysis

Statistical analysis is performed using SPSS (version 26.0, IBM Corp) and the statistical significance level is set at *P*=.05. Continuous variables are explored for normality by the Shapiro-Wilk test to calculate the appropriate descriptive statistics. Continuous variables that are approximately normally distributed are reported as means (SDs) whereas those that are not normally distributed as medians and IQRs (Q1-Q3, where Q1 and Q3 are the first and the third distribution quartiles, respectively). Neuropsychological data expressed as raw scores are treated as continuous variables. Categorical data are described as frequencies and percentages.

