Next, the algorithm with the best-performing pipeline in the 3-fold CV is selected as the proposed method. The general performance of our system on unlabeled data is estimated by evaluating the predictive performance of the proposed method that consists of a fully trained pipeline on the test set. The performance of the ML system is also evaluated based on methods other than the proposed one. The following learning algorithms were applied: k-nearest neighbors (kNN) [37], logistic regression (LogReg) [38], support vector machine (SVM) [39], random forest (RF) [40], ridge classifier (RC) [41], passive aggressive classifier (PAC) [42], stochastic gradient descent (SGD) [43], and naïve Bayes (NB) [44]. For each classifier, we tuned its most important parameters using grid-search CV on a sufficient range of parameter values. The objective of the optimization is to maximize the micro-*F1* score across all validation folds. In addition, we report the performance metrics of accuracy, precision, recall, and *F1* scores.

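### Table 4's confidence intervals are degenerate or too narrow for a test set of 7 or 8 children, with level and method unstated; valid 95% accuracy intervals include the no-information rate

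*Protocol article*

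**What the plan says.** Under Results, Gameplay Data, the article splits 30 participants with usable data into 22 for training and 8 for testing, and says: "we evaluate the predictive performance on a test set consisting of data gathered from 8 (27%) participants using point estimates and CIs". Table 4 prints these figures for the SVM:

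- accuracy 0.85 (0.71-1.00)
- precision 0.75 (0.50-1.00)
- recall 1.00 (1.00-1.00)
- F1 0.85 (0.66-1.00)

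Naive Bayes and logistic regression also carry a recall of 1.00 (1.00-1.00). Neither the level nor the method of the intervals is given. The nearest statement, under Statistical Analysis, is that the "statistical significance level is set at *P*=.05".

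The abstract attributes "accuracy up to 0.85" to the trained models in the plural, without an interval or the size of the test set. It concludes that there is a "notable capacity to discriminate player gameplay behavior as either ADHD or non-ADHD", and the Discussion repeats this. The article also hedges: it calls the analysis preliminary, and both Gameplay Data and the Discussion say that a larger data set is needed.

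**The concern.** A zero-width interval from a handful of children claims certainty about recall that the data cannot give. The SVM accuracy interval matters more. Its printed lower limit, 0.71, lies above the score of a rule that ignores the game and always answers non-ADHD, so a reader takes the classifier to be reliably better than chance. If a valid interval includes that score, the error bars create the impression, and the conclusion about discrimination loses its support. The children behind the table must also be counted first, because the table's own decimals do not fit the number stated in the text.

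**Working it through.** **1. Test denominator.** The test accuracies in Table 4 are 0.28, 0.42, 0.57 and 0.85. Truncated to two decimals, 2/7 = 0.285, 3/7 = 0.428, 4/7 = 0.571 and 6/7 = 0.857 give all four. No other size from 4 to 12 does. With 8 children, 0.85 is impossible: 6/8 = 0.75 and 7/8 = 0.875.

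**2. SVM table.** With n = 7, accuracy 0.85, precision 0.75 and recall 1.00 have one solution: 3 true positives, 0 false negatives, 1 false positive and 3 true negatives. Check: (3+3)/7 = 0.857; 3/(3+1) = 0.75; 3/3 = 1; F1 = 2×3/(2×3+1+0) = 0.857. The class split is 3 ADHD and 4 non-ADHD.

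**3. Training denominator.** The validation accuracies in Table 3 are 0.6190 = 13/21, 0.5238 = 11/21, 0.5714 = 12/21, 0.6667 = 14/21 and 0.4286 = 9/21. Multiplied by 22 they are not whole numbers (0.6190 × 22 = 13.6; 0.6667 × 22 = 14.7). The validation recalls 0.7778, 0.5556 and 0.8889 are 7/9, 5/9 and 8/9, which fits 9 ADHD and 12 non-ADHD. Then 21 + 7 = 28, against the stated 30.

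**4. Trying to reproduce the printed intervals.** A percentile bootstrap of the table in step 2 gives:

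| SVM | Printed | Bootstrap 95% | Bootstrap 80% |
|---|---|---|---|
| Accuracy | 0.71-1.00 | 0.57-1.00 | 0.71-1.00 |
| Precision | 0.50-1.00 | 0.25-1.00 | 0.50-1.00 |
| Recall | 1.00-1.00 | 1.00-1.00 | 1.00-1.00 |
| F1 | 0.66-1.00 | 0.40-1.00 | 0.67-1.00 |

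For accuracy this can be checked directly. Resampling 6/7 gives P(X ≤ 3) = 0.010 and P(X ≤ 4) = 0.065 for X ~ Bin(7, 6/7), so the 2.5th percentile is 4/7 = 0.57, not 5/7 = 0.71. The printed row is not reproduced at 95% with many resamples. The zero-width recall arises because every resample of 3 correct out of 3 is again all correct.

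**5. Valid 95% intervals** (95% is an assumption, taken from the .05 significance level):

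| SVM | Count | Printed | Clopper-Pearson | Wilson |
|---|---|---|---|---|
| Accuracy | 6/7 | 0.71-1.00 | 0.42-1.00 | 0.49-0.97 |
| Recall | 3/3 | 1.00-1.00 | 0.29-1.00 | 0.44-1.00 |
| Precision | 3/4 | 0.50-1.00 | 0.19-0.99 | 0.30-0.95 |

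For k = n the exact lower limit is (0.025)^(1/n), so for recall (0.025)^(1/3) = 0.29. A true recall of 0.50 would give 3/3 with probability 0.5³ = 0.125.

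**6. Benchmark for accuracy.** Always answering non-ADHD scores 4/7 = 0.57, inside both accuracy intervals. The exact one-sided tail is P(X ≥ 6 | n = 7, p = 4/7) = 0.12.

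**7. Sensitivity.**

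- *Test set of 8.* If 7 of 8 were correct, the exact 95% interval is 0.47-1.00. Assuming 5 of the 8 are non-ADHD, P(X ≥ 7 | n = 8, p = 5/8) = 0.14.
- *90% level, 6/7.* The lower limits are 0.48 (exact) and 0.55 (Wilson), still below 0.57.
- *80% level, 6/7.* The exact limit (0.55) stays below 0.57; the Wilson limit (0.62) does not.

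**The case against.** Several points on the other side stand.

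- **The counts are reconstructed.** The text says 8 and 22; 7 and 21 are inferred from decimals. This is why reconciliation comes first. The conclusion about accuracy holds at 7, and at 8 under the assumed split.
- **The article hedges.** It says preliminary, calls the results indicative and asks for more data. That softens the fault, but the statement of a notable capacity in the abstract's Conclusions and in the Discussion is itself unqualified.
- **The level is unstated**, so 95% is an assumption; step 7 shows where it matters.

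Some stronger readings are tempting and are not supported.

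- *The SVM was picked on its test result.* The ML Methodology section reserves the test set for evaluation, and Gameplay Data reports selection on validation F1 and fit. The fair complaint is the plural attribution and the missing interval in the abstract.
- *The rows use different levels, because the same 3/7 accuracy has 0.14-0.85 for some models and 0.14-0.71 for others.* Resampling 3/7 gives at least 6/7 with probability 0.0274, so the 97.5th percentile sits on an edge and ordinary Monte Carlo noise can produce both. The match of the SVM row to an 80% bootstrap is likewise a guess about an unstated method.
- *Recall is no better than chance.* The 0.57 benchmark belongs to accuracy. An always-ADHD rule has recall 1.00, as the test rows for naive Bayes and logistic regression show.
- *Precision of 0.75 misleads about screening.* The article does not present it as a predictive value in a screening population, and a projection would rest on the specificity of four children.

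**Conclusion.** The point holds for the intervals and for what is concluded from them. The recall interval 1.00-1.00 is degenerate; the exact 95% interval for 3/3 is 0.29-1.00. The SVM accuracy interval starts at 0.71 where the exact limit is 0.42 and the Wilson limit 0.49, and so wrongly excludes the no-information rate of 0.57. Against that rate the evidence is P = 0.12 one-sided, or 0.14 if 7 of 8 were correct and 5 of the 8 are non-ADHD. This rests on the reconstructed table and an assumed 95% level. A reader might infer that the game does not discriminate; the data do not show that either. With so few children, discrimination above chance is neither shown nor ruled out.

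**What to change.** 1. Reconcile the test set (7 or 8) and the training set (21 or 22), and state the ADHD and non-ADHD numbers in each.
2. In Table 4, replace the intervals for accuracy, precision and recall by exact or Wilson intervals, with the counts and a stated level and method. F1 is not a simple proportion, so these methods do not apply to it directly.
3. Give the majority-class benchmark next to accuracy.
4. In the abstract, attribute the 0.85 to the selected SVM, with its count and interval; if 7 is confirmed, this is 6/7 with an exact 95% interval of 0.42-1.00. If the cross-validated score (0.6667) is also reported, label it as the score used for tuning and selection, and hence optimistic.
5. Reword the abstract's Conclusions and the matching sentence in the Discussion to say that feasibility was shown and that discrimination is not yet established.

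The work is a short recalculation and a few sentences. The real cost is a less favourable claim.

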## Discussion

Limitations of the existing screening procedures for ADHD diagnosis are summarized as high dependence on pen-and-paper practices, subjectivity bias, difficulty in monitoring in different settings, and risk of data loss. The ADHD360 platform, consisting of the serious game “Pizza on Time” and the mADHD360 app, attempts to offer a holistic technological solution for early detection of ADHD characteristics and serve as a training tool against ADHD-related symptoms. It facilitates real-time data collection in different settings and from different individuals involved in the user’s care. Moreover, the ADHD360 platform enables quantitative data analysis assessing the behavior and game performance of the user while providing a more integrated view of the user's behavioral characteristics. Investigating different state-of-the-art ML methods revealed that our platform is characterized by a notable capacity to discriminate players based on their in-game patterns as those who have ADHD characteristics and those who do not. Thus, it is expected to serve as a complementary screening tool benefiting health care professionals, educators, and people with ADHD.

However, the health emergency imposed by COVID-19 affected the implementation of pilot trials by forcing adaptation of the protocol to remote conditions. Moreover, lockdowns and social distancing may have contributed to the low sample size and the high number of dropouts during the study. Additionally, the long duration of the experimental protocol and the need for commitment to the study procedures may have negatively affected users’ adherence to pilot trials. Moreover, ADHD has been characterized by “a dislike of mental effort” [45]. Considering the aforementioned limitations, we recruited about twice as many participants as originally intended. However, the dropout rate was approximately 30% (13 participants), as 30 participants (70%) completed the first part of pilot phase remotely.

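### Tables 3 and 4 cannot come from the stated 22/8 split of 30 participants; they fit 21 training and 7 test, so the headline accuracy of 0.85 is 6 of 7

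*Protocol article*

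**What the plan says.** All references are to the Protocol article.

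- **ML Methodology** plans "train-test splitting with a 75:25 split ratio", with 3-fold cross-validation inside the training part.
- **Results, Gameplay Data** reports "insufficient or no data generation in 13 of the 43 participants (30"%), and then that "gameplay data collected from 30 (70%) participants were used in the following preliminary analysis". It describes a "training set consisting of data collected from 22 of the 30 participants (73"%) and a "test set consisting of data gathered from 8 (27%) participants using point estimates and CIs".
- **Table 3** gives cross-validation results for eight classifiers to four decimals. **Table 4** gives their test results to two decimals.
- **Abstract, Results** draws its headline from Table 4: "the trained ML models achieve high performance (ie, accuracy up to 0.85").
- **Discussion** states that "the dropout rate was approximately 30% (13 participants), as 30 participants (70%) completed the first part of pilot phase remotely".

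No section mentions 28 participants or any exclusion after the 30.

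**The concern.** A proportion based on a handful of people can take only a few values, so the printed metrics reveal their own denominator. Here that denominator disagrees with the text in both tables. The figure affected is the one that carries the abstract's conclusion on discriminating ADHD from non-ADHD gameplay. A reader who takes the text at face value believes that 30 children were analysed and that 0.85 was obtained on 8. The tables describe 28 children and a result on 7, with no account of the other two.

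**Working it through.** **1. The stated split.** 30 × 0.75 = 22.5, which gives 22 and 8 (73% and 27%). The text is coherent on its own. By comparison, 28 × 0.75 = 21 exactly, leaving 7.

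**2. Table 4 against n = 8.** Accuracy = (TP + TN)/n. With n = 8 the values near those printed are 0.25, 0.375, 0.5, 0.625, 0.75 and 0.875. None gives 0.28, 0.42, 0.57 or 0.85 by rounding or by truncation. A search over every confusion matrix, matching accuracy, precision, recall and F1 together, finds no solution at n = 8 for any of the eight rows.

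**3. Table 4 against n = 7.** With 3 ADHD and 4 non-ADHD, every row has exactly one solution:

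| Classifier | TP | FP | FN | TN | Accuracy | Printed |
|---|---|---|---|---|---|---|
| NB, LogReg | 3 | 4 | 0 | 0 | 3/7 = 0.4286 | 0.42 |
| k-NN, SGD | 1 | 2 | 2 | 2 | 3/7 = 0.4286 | 0.42 |
| PAC | 2 | 4 | 1 | 0 | 2/7 = 0.2857 | 0.28 |
| RF, RC | 2 | 2 | 1 | 2 | 4/7 = 0.5714 | 0.57 |
| SVM | 3 | 1 | 0 | 3 | 6/7 = 0.8571 | 0.85 |

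For SVM, precision = 3/4 = 0.75, recall = 3/3 = 1.00 and F1 = 2×3/(2×3 + 1 + 0) = 6/7, all as printed. Among test sizes from 4 to 30, only 14, 21 and 28 also fit all eight rows. None of them can sit beside a training set of 21 or 22 within 30 participants (21 + 14 = 35 is already too many).

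**4. Table 3 against three folds of 7.** Validation accuracies × 21:

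| Printed | × 21 | × 22 |
|---|---|---|
| 0.4286 | 9 | 9.43 |
| 0.5238 | 11 | 11.52 |
| 0.5714 | 12 | 12.57 |
| 0.6190 | 13 | 13.62 |
| 0.6667 | 14 | 14.67 |

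Training accuracies × 42 (three training portions of 14) are 24, 26, 28, 31 and 32. With 3 ADHD children in each fold of 7, accuracy, precision and recall are reproduced for all eight classifiers, in both training and validation. SGD shows this by hand. Its recall of 1.0000 means TP = 3 in each fold. False positives of 2, 2 and 3 give accuracy (21 − 7)/21 = 0.6667 and mean precision (3/5 + 3/5 + 3/6)/3 = 0.5667, as printed. Every other ADHD layout over folds of 7 fails at least one row.

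**5. Could Table 3 be a mean over unequal folds of 8, 7 and 7?** This has to be tested separately, because multiplying by 22 checks only a pooled proportion. Let a be the number correct in the fold of 8, and b and c the numbers correct in the folds of 7. Mean accuracy = (a/8 + b/7 + c/7)/3, and each of the five printed values then requires a = 0 or a = 8. Two rows rule this out:

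- LogReg has recall 0.0000 and SGD has 1.0000 on the same folds, so every fold contains at least one ADHD child.
- LogReg finds none of them, so it cannot be right on all of the fold of 8. Hence a = 0, and 0.5714 needs b + c = 12. Those 12 are non-ADHD children, which leaves 2 ADHD children in the two folds of 7, one in each.
- SGD finds every ADHD child, so a = 8 and precision in that fold is 1. Then 0.6667 needs b + c = 7, so there are 7 false positives among the 12 non-ADHD children.
- Mean precision 0.5667 requires the three fold precisions to sum to 1.70, so the two folds of 7 must sum to 0.70. The possible splits of the 7 false positives give 1/2 + 1/7 = 0.64, 1/3 + 1/6 = 0.50 and 1/4 + 1/5 = 0.45. None fits.

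A full search agrees: no layout of 8/7/7 satisfies LogReg and SGD together, and none fits more than four of the eight validation rows. Training sizes of 19, 20 and 23 also fail.

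**6. Totals.** Training has 9 ADHD and 12 non-ADHD; test has 3 and 4. Together that is 28: 12 ADHD and 16 non-ADHD. Not analysed: 43 − 28 = 15, and 15/43 = 34.9%. The stated figure is 13/43 = 30.2%.

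**The case against.** The best defence is that little changes. The headline value survives, since 6/7 = 0.857 is printed as 0.85. The intervals are already wide (SVM accuracy 0.71-1.00), the analysis is called preliminary, and the article itself asks for a larger data set. All of that stands, and the choice of SVM is not affected. It does not make the denominator right: the text gives 8 and 30 where the results show 7 and 28.

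A reader might infer four stronger things, none of which the article supports:

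- *That 13 of 43 is itself wrong.* The tables say nothing about technical failures. Thirteen such losses and two later, unreported exclusions would be consistent. What the tables contradict is that 30 were analysed.
- *That two children were removed after their results were seen.* Nothing in the text points to this; an earlier data cut would explain the tables equally well.
- *That the true accuracy might be 6/9 = 0.67.* This puts both extra children in the test set, against the stated 22/8. At most one belongs there. With the classifier held fixed, the result would be 6/8 = 0.75 or 7/8 = 0.875, and even that ignores the refit with a 22nd training child.
- *That nobody completed in person, and that this is an error.* The Discussion's subtraction does imply that all 30 completers were remote, but the COVID-19 adaptation makes that possible.

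Some Table 4 interval limits, such as 0.13 and 0.27, are not sevenths. The interval method is not stated, and these limits may be interpolated percentiles. The point estimates do not depend on them.

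**Conclusion.** The contradiction is certain. A split of 22 and 8 cannot produce Tables 3 and 4, while 21 and 7 produce every row of both. The headline accuracy is 6 of 7, so one child is worth 1/7, or 14 percentage points, and two of the 30 participants said to be used are not in the results. If the tables stand, 15 of 43 (35%) were not analysed. This rests on three assumptions: that Table 4 values are rounded or truncated to two decimals, that Table 3 values are means over three near-equal folds, and that the metrics have their usual definitions. Whether the text or the tables need changing cannot be decided from the article.

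A minor related point: Gameplay Data attributes 13 losses to technical difficulties, while the Discussion calls 13 participants dropouts and derives them from remote completion. These may be the same people under two labels, but the article does not say so.

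**What to change.** Check the analysis data set first, then take one of two routes:

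1. **If the tables are right:** change Gameplay Data to 21 training and 7 test participants (28 analysed; 12 ADHD, 16 non-ADHD), state why the other two were not included, report 15 of 43 (35%) as not analysed, and correct the 30 in the Abstract.
2. **If 30 is right:** re-run the pipeline on all 30 with the 22/8 split, and replace Tables 3 and 4 and the accuracy in the Abstract.

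In either case, report the headline as a count with its denominator (6/7 = 0.86 if the current tables stand). Also give one participant flow by group that separates technical failure, dropout and any later exclusion, so that Gameplay Data and the Discussion agree.

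The first route costs a data check and corrected text. The second adds one re-run on a small data set, after which the headline may move in either direction.
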